### Primary study endpoints

The primary study endpoint measured in the children at two years’ corrected age is the combined incidence of death or cerebral palsy defined as stillbirths, death of live born infant before hospital discharge or death after hospital discharge before two years’ corrected age; or any cerebral palsy [abnormality of tone with motor dysfunction].

### Secondary study endpoints

#### For the infant

•Health outcomes considered to be important measures of mortality and morbidity prior to primary hospital discharge; (defined as stillbirth and death of liveborn infant before hospital discharge; IVH, severe IVH, cystic PVL, neonatal encephalopathy, neonatal convulsions, proven necrotising enterocolitis, retinopathy of prematurity needing treatment, patent ductus arteriosus needing treatment, respiratory distress syndrome, severity of any neonatal lung disease, chronic lung disease (oxygen dependent at 36 weeks post-menstrual age or 28 days of life if born after 32 weeks gestation), use of respiratory support, airleak requiring drainage, confirmed infection within the first 48 hours, infection after the first 48 hours, body size at birth (weight, length, head circumference) and at discharge home).

•Composite serious health outcome (defined as stillbirth and death of liveborn infant before hospital discharge severe respiratory disease, severe intraventricular haemorrhage (grade 3 & 4); chronic lung disease (oxygen dependent at 36 weeks post-menstrual age or 28 days of life if born after 32 weeks gestation); proven necrotising enterocolitis; severe retinopathy of prematurity (Stage 3 or worse in the better eye); cystic periventricular leukomalacia).

#### For the child

Key health outcomes assessed at two years’ corrected age:

•Individual components of the primary outcome including severity of cerebral palsy (defined as death; cerebral palsy).

•Death or any neurosensory disability (*death* defined as stillbirth, death of live born infant before hospital discharge or death after hospital discharge; and *any neurosensory disabilities* that includes the neurosensory impairments of *cerebral palsy,* [GMFCS level 1 to 5], *blindness* [corrected visual acuity worse than 6/60 in the better eye], *deafness* [hearing loss requiring amplification or worse], and any *developmental delay* defined as standardised score more than 1 SD below the mean (< −1SD).

•Death or major neurosensory disability. Major neurosensory disability includes *severe and moderate disability* (defined as any of: legal blindness, sensorineural deafness requiring hearing aids; moderate or severe cerebral palsy [GMFCS level 2 to 5] or developmental delay/intellectual impairment [standardised score more than two SD below the mean].

•General health of the child (including use of health services since primary hospitalisation), *childhood respiratory morbidity, blood pressure* (Z scores and proportions in hypertensive ranges), *behaviour* as assessed by the Child Behaviour Checklist [54] and body size.

#### For the mother

•Maternal serious adverse cardiovascular and/or respiratory outcome of the infusion (defined as maternal death, cardiac arrest, respiratory arrest).

•Maternal side effects of the infusion (including nausea; vomiting; flushing, infusion arm discomfort; mouth dryness; sweating; dizziness; blurred vision; respiratory rate decreased > four breaths per minute below baseline or <12 breaths per minute; blood pressure decreased > 15 mmHg below baseline level; whether the infusion is discontinued because of side effects).

•Incidence of postpartum haemorrhage, estimated blood loss at birth 500 ml or more; and major postpartum haemorrhage, estimated blood loss 1500 ml or more; mode of birth.

### Sample size

The rate of our primary outcome of death or cerebral palsy at two years’ corrected age in an Australian/New Zealand population between 30 to 34 weeks’ gestation is estimated to be 9.6%, using a predicted mortality rate up to 2 years of age of 4.4% (excluding lethal anomalies) [57] and a predicted rate of cerebral palsy in survivors of 5.2% [46,48].

A trial of 1676 children (838 per group), allowing for a design effect of 1.2 for clustering of babies within mothers and a 5% loss to follow up, with an absolute risk difference of 4.2% [45,46,48] will have 80% power to detect a statistically significant difference at an alpha level of 0.05 (two-tailed) of a decrease in the combined outcome of death or cerebral palsy from 9.6% to 5.4% with magnesium sulphate compared with placebo.

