## Background

Babies born preterm have a higher chance of dying in the first few weeks of life than those born at term [1]. Babies who survive have a greater risk of neurologic impairments, such as cerebral palsy, blindness, deafness, or cognitive dysfunction, and a greater risk of substantial disability as a result of these neurologic impairments [2-4]. The social and economic long-term costs are considerable [5].

Cerebral palsy is a term which includes a number of different diseases or conditions that can arise at any time during brain development. It involves a disorder of movement or posture, or both, and a disorder of motor function that is permanent but may change over time [6]. The cerebral palsies remain the most frequent cause of severe motor disability in childhood with a background prevalence of two per thousand live births [6]. Most affected children (92%) survive to 20 years or later, yielding a substantial burden of illness into adulthood [7].

Very preterm birth (less than 34 weeks) is the principal risk factor for cerebral palsy [8,9], responsible for 17% to 32% of all cases of cerebral palsy. The latest Australian Cerebral Palsy Register Report (2009) shows that approximately 45% of all cases of cerebral palsy are associated with preterm birth [10]. Whilst the highest risks are for extremely preterm infants [3], babies born between 30 and 33 completed weeks’ gestation still have significant risks [11] with the risk of cerebral palsy being up to eight times more likely than babies born at term [4]. Moderate prematurity is responsible for as many cases of cerebral palsy as extreme prematurity [10].

At present there is no cure for cerebral palsy, which makes effective preventative interventions of paramount importance. Prevention of cerebral palsy has been identified by consumers, clinicians and researchers as a top priority for research by the Australian Cerebral Palsy Institute [12]. To reduce the impact of cerebral palsy from preterm birth, efforts must be focused on primary prevention.

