### Results of the meta-analysis of the Cochrane systematic review

The combined outcome of death or cerebral palsy or cerebral palsy alone showed significant reductions where women who were at risk of preterm birth were given magnesium sulphate antenatally with the intent of providing neuroprotection (Table 1). The review showed that 63 babies (95% CI 44 to 155) need to be treated with magnesium sulphate for one baby to avoid cerebral palsy. The corresponding number needed to treat to benefit (NNTB) for combined death or cerebral palsy was 42 babies, 95% CI 24 to 346.

**Table 1 T1:** **Magnesium sulphate vs placebo/no treatment: primary outcomes**[33]

**Primary outcomes**	**RR, 95% CI**	**Number of trials; participants**
**Death or cerebral palsy**	0.85, 0.74 to 0.98*	four trials; 4446 infants
**Death (fetal and later)**	0.95, 0.80 to 1.12	four trials; 4446 infants
**Cerebral palsy**	0.71, 0.55 to 0.91*	four trials; 4446 infants
**Any neurological impairment**	1.03, 0.87 to 1.21	one trial; 1255 infants
**Death or substantial gross motor dysfunction**	0.84, 0.71 to 1.00	three trials; 4387 infants

*Significantly in favour of magnesium sulphate.

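### The 5.2% cerebral palsy rate behind the 9.6% control rate is not reconciled with the protocol's own Background figures, and the 80% power holds only if 9.6% is right

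*Protocol article*

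**What the plan says.** The Sample size section of the protocol article estimates the control rate of death or cerebral palsy at two years' corrected age as 9.6%. It adds a mortality of 4.4% to "a predicted rate of cerebral palsy in survivors of 5.2"%, citing references 46 and 48 for the latter. A trial of 1676 children (838 per group), with a design effect of 1.2 and 5% loss to follow-up, "will have 80% power to detect a statistically significant difference" at "an alpha level of 0.05 (two-tailed"), for a fall in "death or cerebral palsy from 9.6% to 5.4% with magnesium sulphate compared with placebo", that is, "with an absolute risk difference of 4.2"%.

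The Background section gives two other figures for cerebral palsy. One is a "background prevalence of two per thousand live births". The other concerns babies born at 30 to 33 completed weeks, "with the risk of cerebral palsy being up to eight times more likely than babies born at term". The same paragraph says that the highest risks are in extremely preterm infants.

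Table 2 shows that the trial in reference 46 was open from viability to under 33 weeks. Reference 48 is mentioned under Two years assessments as a previous trial by this group; its gestational range is not given.

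**The concern.** The weeks to which the eightfold figure applies are exactly this trial's two gestational strata (30 to 31 and 32 to 33 completed weeks, under Study groups). A reader who combines the Background figures reaches a cerebral palsy rate of about 1.6%. The sample size uses a rate more than three times as high, and nothing in the text connects the two.

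The gestational range of reference 46 adds to the doubt, because it takes in births below 30 weeks.

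If the true rate lies well below 5.2%, the trial will see fewer events than planned. A non-significant result could then be read as no benefit at 30 to 34 weeks when the trial had limited power to show one.

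**Working it through.** **Reproducing the stated size.** Inputs from Sample size: p1 = 0.096, p2 = 0.054, two-sided alpha 0.05, power 80%, design effect 1.2, loss 5%. The two-proportion formula gives 617 per group, or 663 with continuity correction. Inflating the latter: 663 x 1.2 / 0.95 = 837.5, so 838 per group and 1676 in total, exactly as stated. Without the correction the total would be 1560. The article names no formula; use of the correction is inferred from this match.

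**The rate implied by the Background.** 8 x 0.2% = 1.6%, and 5.2 / 1.6 = 3.25. As a population estimate this is generous: the all-births prevalence stands in for the term rate, although it includes preterm births, and the upper end of the multiplier is used. Reading eight times more likely as ninefold gives 9 x 0.2% = 1.8%, and 5.2 / 1.8 = 2.9.

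**Combining the components.** The 5.2% is a rate among survivors, so it applies to 95.6% of children: 4.4% + 0.956 x 5.2% = 9.37%, not 9.6%. At 1.6% the same formula gives 4.4% + 0.956 x 1.6% = 5.93%. Cerebral palsy's share of the planned rate, as the protocol adds it, is 5.2 / 9.6 = 54%.

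**Power at 1676 children with the relative risk held.** Planned relative risk = 5.4 / 9.6 = 0.5625. Effective n per group = 838 x 0.95 / 1.2 = 663.4. With d = p1 - p2 and pbar their mean,

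power = Phi{[d - c - 1.96 sqrt(2 pbar(1 - pbar)/n)] / sqrt([p1(1 - p1) + p2(1 - p2)]/n)},

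where c = 1/n with continuity correction and 0 without.

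| Cerebral palsy in survivors | Control rate | Treated rate | Power, corrected | Power, uncorrected |
|---|---|---|---|---|
| 5.2%, simple sum as in the protocol | 9.60% | 5.40% | 80.0% | 82.8% |
| 5.2% | 9.37% | 5.27% | 78.9% | 81.8% |
| 4% | 8.22% | 4.63% | 72.6% | 76.3% |
| 3% | 7.27% | 4.09% | 66.5% | 70.7% |
| 1.6% | 5.93% | 3.34% | 56.3% | 61.4% |

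Expected events among evaluable children (838 x 0.95 = 796 per group): 796 x (0.096 + 0.054) = 119 as planned, and 796 x (0.0593 + 0.0334) = 74 in the last row.

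**Holding the 4.2-point difference instead.** At a 5.93% control rate the treated rate would be 1.73%, a relative risk of 1.73 / 5.93 = 0.29. Nominal power would rise to about 98%, but the effect is hard to credit. Preventing every case of cerebral palsy saves only 0.956 x 1.6% = 1.5 points, so deaths would also have to fall from 4.4% to 1.73%, a 61% reduction. Table 1 gives pooled relative risks of 0.95 (0.80 to 1.12) for death and 0.85 for the composite.

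**The case against.** The strongest reply is that 1.6% does not estimate this trial's endpoint. It multiplies two figures from different sources, and the protocol never states the product. The endpoint is any cerebral palsy found at formal examination of all survivors at two years, and the protocol itself says the diagnosis may not be stable before five years. The women enrolled have birth planned or expected within 24 hours and may carry twins, so their babies are not a general cohort born at 30 to 33 weeks. A rate above the population figure is plausible. This stands: a reader might infer that 1.6% is a maximum, or that 5.2% is shown to be wrong, and the documents support neither. Reference 48 is not described, and either source may have supplied gestation-specific data.

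A reader might also infer that 5.2% was taken over from much less mature babies, because the cited review's finding that "63 babies (95% CI 44 to 155) need to be treated with magnesium sulphate for one baby to avoid cerebral palsy", with its relative risk of 0.71, implies a control rate of (1/63) / 0.29 = 5.5%. That comparison is weak. The 5.5% is per infant, deaths included, while 5.2% is per survivor. The same method applied to the review's composite gives (1/42) / 0.15 = 15.9%, well above 9.6%, so the plan does assume a lower-risk population. The populations also overlap: 32% of the largest trial in the review was not under 30 weeks, and entry there ran to under 32 weeks.

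Finally, the lower power figures depend on holding the relative risk, whereas the protocol states an absolute difference. The planned log binomial analysis is arguably closer to the uncorrected column. Both points are fair, which is why both columns and the absolute-difference case are shown. Below 5.2% with the relative risk held, neither column reaches 80% at any rate examined (4%, 3% and 1.6%).

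**Conclusion.** The point holds as an unreconciled input. The rate that supplies over half of the planned control events is about three times what the Background figures imply for the same weeks of gestation, and the article does not say why.

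A reader might go further and conclude that the 80% is miscalculated. It is not: it reproduces exactly for 9.6% against 5.4%. What the documents do not establish is that 9.6% applies to this population. At a fixed relative risk of 0.5625 and mortality of 4.4%, power is about 73-76%, 66-71% and 56-61% for cerebral palsy at 4%, 3% and 1.6% of survivors. The loss is moderate at intermediate rates and serious only towards the bottom of the range. Adding a survivor rate directly to mortality is a small separate slip, worth about one percentage point of power.

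None of this biases the treatment estimate or affects the type I error. It bears on how much weight the stated power, and later a null result, can carry.

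**What to change.** In Sample size, either replace 5.2% with a rate specific to 30 to 33 completed weeks or say why 5.2% is appropriate given the Background figures, including which gestations in references 46 and 48 it comes from. Combine the components as 4.4% + 95.6% x the survivor rate, which gives 9.4% if 5.2% is kept. Restate power for 1676 children over a range of control rates, for example 5.9%, 7.3% and 9.4%, at a fixed relative risk, and carry any changed control rate into the abstract.

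A blinded check of the pooled event rate is optional. It needs no unblinding and no alpha, but it would inform slowly because cerebral palsy is assessed at two years.

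The cost is a few sentences and a less favourable power statement. No extra participants are needed.

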### Analysis and reporting of results

Data will be analysed by a statistician independent of the clinical investigators. Potential confounding variables will comprise socio-demographic variables, such as ethnicity, language spoken at home, family structure, mother’s marital status, social class, and mother’s and father’s education, as well as gender of the baby. Comparisons will be made between treatment groups for the primary and secondary endpoints using an intention to treat approach. Analyses will make adjustments for the stratification variables and for important baseline predictors including gestational age at birth, and reasons for risk of preterm birth. Log binomial regression and linear regression will be used to examine dichotomous and continuous outcomes respectively with results presented as relative risks or differences in means along with 95% confidence intervals. Adjustment till be made for clustering due to multiple births for infant outcomes using generalized estimating equations. *P*-values <0.05 will be considered statistically significant.

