### Inclusion criteria

Women are eligible for the trial if they are at risk of preterm birth between 30 to 34 weeks’ gestation where birth is planned or definitely expected within 24 hours, have a singleton or twin pregnancy, no contraindications to the use of antenatal magnesium sulphate (respiratory depression, hypotension, renal failure, myasthenia gravis) and give informed, written consent.

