### Study groups

Once all entry details are given and eligibility is confirmed, the woman is randomised by contacting the central telephone randomisation service at the University of Adelaide. Assignment to one of two study groups: either the magnesium sulphate group or the placebo group will be stratified for collaborating centre, gestational age (30 to 31 completed weeks; 32–33 completed weeks’ gestation), and number of fetuses (1 or 2). A Study Number is allocated to the woman corresponding to a treatment pack, each of which looks identical and contains a 100 ml infusion bag.

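### Treatment comparisons adjust for gestational age at birth as a baseline predictor, although it is fixed only after randomisation and infusion

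*Protocol article*

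**What the plan says.** In the protocol article, Analysis and reporting of results sets one covariate rule. Besides the factors used to stratify randomisation, it requires adjustment "for important baseline predictors including gestational age at birth, and reasons for risk of preterm birth". The sentence before it reads: "Comparisons will be made between treatment groups for the primary and secondary endpoints using an intention to treat approach". As written, the rule therefore covers the primary endpoint, which Primary study endpoints gives as "the combined incidence of death or cerebral palsy defined as stillbirths, death of live born infant before hospital discharge or death after hospital discharge". The period runs to the two-year assessment, and cerebral palsy of any severity also counts. The model is also named: "Log binomial regression and linear regression will be used to examine dichotomous and continuous outcomes respectively", with relative risks reported and generalised estimating equations for multiple births.

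On timing, Inclusion criteria admits women "at risk of preterm birth between 30 to 34 weeks’ gestation where birth is planned or definitely expected within 24 hours". Study groups has assignment "stratified for collaborating centre, gestational age (30 to 31 completed weeks; 32–33 completed weeks’ gestation), and number of fetuses (1 or 2". The infusion follows randomisation.

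The article gives no reason for including gestational age at birth. It does not present the adjustment as a sensitivity or mediation analysis, and it names no comparison that omits it.

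**The concern.** A covariate in a randomised comparison should be settled before allocation, so that treatment cannot have influenced it. Gestational age at birth does not meet that test: at randomisation the birth has not yet happened. Its value may depend on the infusion, on decisions taken after allocation, and on unmeasured factors that bring birth forward and also affect the child. For a stillborn child, who counts as a primary event, the time of birth may itself follow from the death.

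At stake is which effect is estimated. Aims and objectives and Hypotheses ask whether giving magnesium sulphate reduces death or cerebral palsy. That is a total effect, and it matches the intention-to-treat approach. Holding gestational age at birth constant answers a different question if treatment moves the time of birth. The rule makes no exception for secondary endpoints either. Body size at birth, for example, would be adjusted for gestation at birth, which takes out any effect through timing.

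**Working it through.** **1. The plan's own figure.** Inputs from Sample size: 9.6% v 5.4%, two-sided alpha 0.05, 80% power, design effect 1.2, 5% loss. The pooled-variance formula for two proportions gives 617 per arm, or 663 with continuity correction. Then 663 × 1.2 / 0.95 = 837.5, rounded up to 838 per arm, 1676 in total. The stated number reproduces. It uses no covariates, so this point does not change it. The design relative risk (RR) is 0.054 / 0.096 = 0.5625.

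**2. Order of events.** Eligibility (birth still ahead), then randomisation by gestational-age stratum, then infusion, then birth. The stratum is baseline; gestational age at birth is not.

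**3. When the adjustment matters.**
- *Treatment does not alter time to birth.* Gestational age at birth is then independent of allocation, and conditioning on it links allocation to no other cause of the outcome. The treatment RR is not biased.
- *Treatment alters time to birth.* The adjusted RR leaves out the part that acts through timing. If an unmeasured factor affects both timing and outcome, conditioning on timing also links allocation to that factor.

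**4. Size at shifts that fit the entry rule.** The documents give no latency effect and no risk gradient by week, so both are assumptions here. If risk falls by a fraction f per week and treatment delays birth by d days, the mediated RR = (1 − f)^(d/7).

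| Delay | f = 15% | f = 20% |
|---|---|---|
| 12 hours | 0.85^(0.5/7) = 0.988 | 0.80^(0.5/7) = 0.984 |
| 24 hours | 0.85^(1/7) = 0.977 | 0.80^(1/7) = 0.969 |

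If the total RR were the design value and effects multiply, the adjusted RR at f = 20% would be 0.5625 / 0.984 = 0.57 for 12 hours and 0.5625 / 0.969 = 0.58 for 24 hours. This is the mediated part only; a shared cause would add to it.

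**5. Larger shifts, for the pattern only.** A large-sample simulation with a log link used a direct RR of 0.5625, entry gestation spread over 30 to 34 weeks, mean latency of about 1 week on placebo, and a log-risk slope of 0.15 or 0.20 per week. Some scenarios added an unmeasured factor affecting both latency and outcome. Total RR, then RR adjusted for stratum and gestational age at birth:
- no shift: 0.565 and 0.565; with the shared factor, 0.560 and 0.560
- about 0.3 week: 0.539 and 0.560; with the shared factor, 0.546 and 0.576
- about 0.5 week, shared factor: 0.534 and 0.591
- about 1 week, shared factor: 0.510 and 0.613 (slope 0.15); 0.494 and 0.608 (slope 0.20)

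Adjusting for the entry stratum alone returned the total RR in every scenario. These latencies sit poorly with the entry rule: 0.3 week is about 2.1 days, and a mean of 1 week is seven times the 24-hour window. They show how the bias behaves, not what to expect in this trial.

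**The case against.** The strongest reply is that nothing in the article says magnesium sulphate changes the time to birth. The section on biological plausibility describes neuroprotective and haemodynamic mechanisms, the hypotheses do not include prolonging pregnancy, and time to birth is not a listed outcome. Entry requires birth within about a day, followed by a single 30-minute infusion, so gestation at entry and at birth should nearly coincide. Gestation is also likely to be prognostic, the two entry strata are coarse, and the article does not say whether an adjusted or an unadjusted estimate is primary.

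Most of this stands as a limit on size. It does not rescue the variable. Expected birth is not the same as birth, and the article does not exclude an effect on timing. Where entry and birth gestation agree, using the entry value loses little. Where they differ, only the entry value is safe. The rule as written reaches the primary endpoint, whichever estimate is later named as primary.

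A reader might go further and infer that the adjustment by itself opens collider bias, undoes randomisation, or could reverse the direction of the result. The documents do not support this. Bias in the treatment effect needs an effect of treatment on timing, which they neither state nor exclude. A reversal would need several further inputs at once, such as a prolongation of days and a strong unadjusted shared cause. None of these is documented, and the planned adjustment for the reason for risk of preterm birth may close part of such a path.

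**Conclusion.** The point holds in conditional form. Calling gestational age at birth a baseline predictor is wrong on the article's own sequence of events, and no other section corrects it. Whether the treatment estimate is biased depends on whether treatment alters time to birth. If it does not, there is no bias. If it does, the adjusted RR is not the total intention-to-treat effect.

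The size is unknown. Under an assumed fall in risk of 15% to 20% per week and a shift of 12 to 24 hours, the mediated RR is about 0.97 to 0.99, which is small beside a design RR of 0.56. A shared cause or a longer shift would make the discrepancy larger. This should be fixed because the correction costs almost nothing; it does not show that the trial's result would be wrong.

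**What to change.** In Analysis and reporting of results, replace gestational age at birth with gestational age at trial entry. This can be the stratum already in the model, or weeks at randomisation if recorded (the article documents only the two strata). State that covariates in treatment comparisons are limited to variables fixed at randomisation. Report gestational age at birth by arm as a description, and label any analysis that adjusts for it as exploratory.

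The cost is one line in the protocol, carried into the analysis plan before unblinding. The stratum is already recorded at randomisation, and the sample size stays at 1676.
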